**Safety (Week 4 and Week 8)**

Secondary outcomes in Stage 1 will include on the safety of the herbal formulation in children aged 6–14 years at Weeks 4 and 8 of the study. Data will be collected from adverse reactions (type, severity, relation to investigational product), and side effects experienced by the participant recorded in the diary. An interim analysis will be conducted after enrolment of 30 participants to assess safety and continuation of the trial. Also at this time point, a power calculation to confirm participant numbers needed to reach statistical significance will determine the total number of participants required for recruitment. Safety data will be continued to be collected throughout Stage 2.

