#### Sample size

To detect a difference between the intervention group and the control group, a calculation from a trial on desmopressin and oxybutynin [38] was conducted. The power calculation used 80% power for 5% significance based on three-month results (*p* = 0.001). This resulted in the number of children required to recruit being 80 participants. This allows for a 20% attrition rate which provides an adequate number of participants in the primary analysis.

Due to the absence of existing studies involving similar populations and interventions, an interim sample size calculation will be conducted to confirm and potentially readjust the sample size as appropriate. The recalculation of the sample size will be conducted after 30 participants have completed the trial. The difference in the change (from baseline) in the frequency of nocturnal enuresis at week 8 will be calculated. This difference will then be imputed into the same equation used for the sample size calculation applied during study design. Any readjustment on the trial recruitment numbers will be resubmitted to the authorising HREC committee with the interim sample size calculation.

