#### Statistical methods

All data will be analysed on STATA©14. Analyses will be conducted on an intention to treat basis. Descriptive and inferential statistics will be conducted. The difference in change between groups will be analysed using paired T-tests and Analysis of Variance (ANOVA). Groups will be compared at baseline and if difference(s) is/are ascertained, the variable(s) will be entered into the regression model to appropriately adjust the analyses. Sensitivity analyses will also be conducted to account for incomplete adherence to protocol. Interim statistical analysis for safety will occur after 30 participants have completed. This is same timing as the re-evaluation of the sample size calculation. All baseline, demographic, safety and efficacy outputs data will be summarised by treatment group. In summary tables of continuous variables, the minimum and maximum statistics the arithmetic mean and median, the 95% confidence interval, standard deviation, and standard error will be presented to the same number of decimal places as the original data. Safety outputs will be documented at the interim analysis and end of trial in columns with number, severity, treatment group and percentage. All hypothesis testing will be carried out at the 5% (2-sided) significance level unless otherwise specified. *P* values will be rounded to three decimal places. *P* values less than 0.001 will be reported as < 0.001 in tables (Table 1).

**Table 1 Tab1:** Details of the active and control interventions

Arms	Assigned Interventions
Active Comparator: Treatment 1 capsule in the morning (≤40 kg) or 2 capsules in the morning (> 40 kg) for 8 weeks duration.	Dietary supplement: Bedtime Buddy Active treatment- Proprietary combination of 420 mg of herbs. expressed as dry herb equivalent: Crateva nurvala 3000 mg (120 mg) *Equisetum arvense* 1500 mg (150 mg) Lindera Aggregata 1500 mg (150 mg)
Control Comparator: Placebo 1 capsule in the morning (≤40 kg) or 2 capsules in the morning (> 40 kg) for 8 weeks duration.	Placebo- Identical vegetarian capsule containing colour-matched cellulose to that of the active treatment

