**Fig. 4 Fig4:**
[figure not shown]
Adverse event flow chart

A Safety Advisory Board overseeing any serious adverse events (SAE) consists of three independent expert representatives (General Practitioner, Pharmacist and Herbal Medicine researcher and scholar). Any SAE’s will assessed by the safety committee with 24 h to determine if the adverse event is attributed to the interventional agent. The ensuing action will be decided between the Safety Advisory Board and the investigators.

In light of new information about the treatment that may arise during the trial, the participant / parent will be notified and it will be discussed with the parent whether they want the child / participant to continue on the trial. If it is decided that the participant will continue in the study, they will be asked to sign an updated consent form. Also, on receiving new information on potential harms, the researchers might consider it appropriate to withdraw specific a participant from the clinical trial. If this happens, the researcher will explain the reasons and arrange for the participant’s regular health care to continue by sending an updated letter to the child’s local medical practitioner.

An interim analysis will be performed on the primary endpoint when 30 participants have been randomised and completed 8 weeks of the intervention.. The interim-analysis will be performed by the PI, blinded for the treatment allocation. The results of the analysis will be discussed with the Safety Advisory Board and the research team in a joint meeting. A re-calculation of the total target sample will be applied based on the interim analysis, with any changes to final intended sample size reported to the ethics committees overseeing the conduct of the project.

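### The sample size is to be reset from the between-group difference seen in about 30 children, an input too noisy for the purpose and mildly inflating type I error, at an interim whose blinding and trigger are stated inconsistently

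*Protocol article*

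**What the plan says.** The Sample size section gives the design basis as follows: "The power calculation used 80% power for 5% significance based on three-month results" of a trial of desmopressin and oxybutynin. This leads to 80 children, including a 20% attrition allowance. No planning difference or SD is stated.

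Because comparable studies are lacking, the same section plans an interim recalculation. It takes the difference in change from baseline in enuresis frequency at week 8, and "This difference will then be imputed into the same equation used for the sample size calculation applied during study design". The Safety outcome paragraph describes the same step: "a power calculation to confirm participant numbers needed to reach statistical significance will determine the total number of participants required for recruitment". No floor, cap or increase-only rule is given. Statistical methods keeps the final test level: "All hypothesis testing will be carried out at the 5% (2-sided) significance level unless otherwise specified".

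The timing is stated in three specific ways:

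- Safety outcome paragraph: "An interim analysis will be conducted after enrolment of 30 participants to assess safety and continuation of the trial".
- Sample size: "The recalculation of the sample size will be conducted after 30 participants have completed the trial". Under Trial duration, participation lasts 32 weeks.
- Monitoring: "An interim analysis will be performed on the primary endpoint when 30 participants have been randomised and completed 8 weeks of the intervention".

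Statistical methods says only that 30 have completed, without saying what, and that the safety interim and the recalculation happen at the same time.

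Monitoring has the principal investigator run the interim blinded to allocation, and then: "The results of the analysis will be discussed with the Safety Advisory Board and the research team in a joint meeting". Allocation concealment mechanism and Implementation say that the principal investigator generates the sequence, and the former adds that the same person seals it.

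**The concern.** The design equation was built to detect a difference between the intervention and control groups, so the quantity fed back into it is the observed treatment effect on the primary endpoint. Three problems follow.

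**Noise.** Required sample size varies with the inverse square of the difference. An imprecise difference therefore gives an erratic sample size, even when the treatment works exactly as planned.

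**Type I error.** The weight of the interim data in the final analysis depends on what those data showed. A favourable interim result is followed by few further children and is barely diluted, while an unfavourable one is followed by many. An unadjusted 5% test then no longer has a 5% error rate.

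**Conduct.** A between-group primary-endpoint result is computed by the person who made the sequence and discussed with staff who go on contacting families. The documents also do not agree on when this happens, so the rule cannot be carried out consistently as written.

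**Working it through.** **1. The planned 80.** It cannot be reproduced, because no difference or SD is given. Back-solving: 80 × 0.8 = 64 evaluable, 32 per arm. With n per arm = 2(1.96 + 0.8416)² / d² = 15.70 / d², setting n = 32 gives d = √(15.70 / 32) = 0.70. This d is an assumption, used below.

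**2. Precision at the interim.** With 15 per arm, SE(d̂) = √(2/15) = 0.365, which is 52% of the assumed effect. The 95% range of d̂ is 0.70 ± 1.96 × 0.365, or −0.02 to 1.42.

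**3. Recalculated total, true d = 0.70, SD taken as known.** Each quantile of d̂ goes into 2 × 15.70 / d̂², rounded up per arm:

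| Quantile of d̂ | d̂ | Evaluable total |
|---|---|---|
| 10% | 0.232 | 584 |
| 25% | 0.454 | 154 |
| 50% | 0.700 | 66 |
| 75% | 0.946 | 36 |
| 90% | 1.168 | 24 (fewer than the 30 already in) |

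Simulations that also estimate the SD, at d = 0.71, put the quartiles at 34 and 142 to 152. The upper tail is unstable: the total exceeded by one trial in ten was 446 in one run and 560 in another. The conclusion does not depend on that tail.

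**4. Type I error.** Simulated under no effect: 15 per arm at the interim, total reset by the formula within a floor and a cap, all data then tested at an unadjusted two-sided 5%. The limits are scenarios, since the protocol gives none. The existing list holds 12 blocks × 8 = 96 allocations, or 96 × 0.8 ≈ 77 evaluable after 20% attrition.

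| Evaluable total allowed | Type I error |
|---|---|
| Fixed at 64 | 5.0% |
| 64 to 76-78 (existing list after attrition) | 5.2-5.4% |
| 64 to 96 | 5.5-5.7% |
| 64 to 2000 | 7.0% |
| 30 to 64 | 5.9% |
| 30 to 96 | 6.5-7.1% |
| 30 to 320 | 7.8-8.0% |
| 30 to 2000 | 7.9% |

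Ranges cover repeated runs, with z- and t-tests where both were done.

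**5. Blinding.** A between-group difference cannot be computed unless the data are split by arm. If the analyst has no grouping at all, the Sample size calculation cannot be done. If the analyst has coded groups, the size of the difference is visible, and this analyst generated the sequence. The two statements need reconciling under either reading.

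**6. Trigger.** For a given child, completing the trial comes 32 − 8 = 24 weeks after completing week 8. Accrual is not stated, so two assumptions are shown, ignoring dropout and using 4.345 weeks per month:

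| Accrual | At 30 enrolled, with week-8 data | Enrolled when 30 finish week 8 | Enrolled when 30 finish week 32 |
|---|---|---|---|
| 80 in 12-18 months | 18-22 | 38-42 | 63-79 |
| 30 in 18 months (termination limit) | about 27 | about 33 | about 42 |

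For example, 30 in 18 months is 1.67 per month. Eight weeks is 1.84 months, so about 3 of 30 lack week-8 data. Thirty-two weeks is 7.36 months, so about 12 more children are enrolled by then.

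**The case against.** **Blinding.** A reader might infer that openly labelled comparative results are handed to the research team and that the trial is thereby unblinded. The documents do not support that. Monitoring says the analysis is done blinded to allocation, Trial design and Blinding keep researchers and assessors masked, and the form of the shared results is not described. Parents, who keep the diary, are not at the meeting, and an aggregate difference reveals no child's allocation. What remains is the conflict in step 5, and an indirect route through staff who know the size of the difference and continue visits, calls and questionnaire help.

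**Type I error.** A reader might also take 7-8% as the trial's error rate. That needs a floor of 30 or a very high cap, and neither is in the protocol. The only provision actually made is upward, in two spare blocks. Limits and a test adjustment could also sit in an analysis plan that is not shown, and any change of size goes to the ethics committees, so the total need not follow the formula mechanically. All this bears on the size of the inflation. It does not change the stated input, and ethics review of a new total does not remove its dependence on the interim effect.

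**Wording.** The phrase about reaching statistical significance describes a power calculation. It is loose wording and should not be read as an intention to recruit until the result is significant.

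**Timing.** That most recruitment would be over when 30 have completed the trial holds at the faster accrual above, but not at the slowest permitted rate.

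**Remedy.** The stated reason for recalculating is an uncertain effect, which a blinded SD cannot resolve. Effect-based re-estimation with a suitably adjusted test is a legitimate alternative. It would still rest on about 15 children per arm.

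**Conclusion.** The concern holds in this measured form. The Sample size section states a rule, and the rule uses the wrong input. At the assumed d of about 0.70, a treatment working exactly as planned would still give a recalculated total anywhere from about 34 to 150 in the middle half of trials.

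The type I error inflation is real but modest. It is about 5.2-5.7% if the total is held at 64 or more and near the existing list, and about 7-8% if it may drop to 30 or rise freely. These figures assume a normally distributed outcome, equal arms and mechanical use of the formula.

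The blinding statement and the planned calculation do not fit together while the same principal investigator generates the sequence and runs the interim. The three triggers are incompatible, because Statistical methods gives the safety interim and the recalculation the same timing. That contradiction needs no assumption, although its practical effect depends on accrual.

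**What to change.** State the planning difference and SD that lead to 80. Then replace the interim rule as follows:

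- When 30 children have completed week 8, estimate only the pooled SD of the primary outcome, without group labels.
- Put that SD into the design formula with the planning difference held fixed. Let the total stay or rise, up to a stated cap.
- Compute no between-arm efficacy difference at the interim. Give by-arm safety tables to the Safety Advisory Board only.
- Use this one trigger in the Safety outcome paragraph, Sample size, Statistical methods and Monitoring.

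In simulation of blinded SD re-estimation at a planning d of 0.70, without the increase-only restriction, type I error was 5.0% and power 0.79. The 10th to 90th percentiles of the total were 50 to 98 when d = 0.70 and 44 to 88 under no effect, against 24 to 584 from the formula in the current rule. Ignoring labels overstates the variance slightly when the effect is real, by a factor of 1 + 0.70²/4 = 1.12, which moves 64 to about 72 and errs on the safe side.

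The cost is mostly wording, plus recovering and stating the planning difference, without which the formula cannot be used. The trial gives up an early view of the effect, which 30 children cannot provide reliably.

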#### Recruitment

Convenience sampling techniques will be used to target the wider social community of parents with children that are experiencing NE. Participants will be recruited from the general population through social media other general recruitment channels. Several strategies will be utilised in the recruitment including magazine advertisements, web page, social media (Twitter and Facebook), primary school newsletters, distribution of advertising flyers placed in a variety of locations (i.e. Wellnation Clinics reception, health food stores and holistic CM clinics in Brisbane). Interested individuals will be directed to contact the Researchers directly via phone or email to express interest in the trial. A participant information sheet is available to download on the trial webpage but also is emailed to potential participants on enquiry.

### Methods: assignment of interventions

A block randomisation allocation was used based on 10 blocks of eight with an allocation of 1:1. Two extra blocks of eight were generated for over 80 allocations.

#### Allocation

##### Sequence generation

A computer-generated number randomisation was utilised: https://www.random.org/. No stratification was implemented due to the specified age restriction of ages 6–14. The block randomisation sequence generated is provided in a separate document that is unavailable to those who enrol participants or assign interventions.

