## Background

Nocturnal enuresis (NE), or ‘bedwetting’, is a form of night time urinary incontinence occurring in younger children [1, 2]. More specifically, primary nocturnal enuresis (PNE) is defined as the involuntary discharge of urine at night in children aged 5 years or older, who do not have congenital or acquired defects of the central nervous system or urinary tract and have not experienced a dry period of more than 6 months [1]. NE is classified as either *monosymptomatic enuresis* – enuresis with no other lower urinary tract symptoms – or *non-monosymptomatic enuresis* – enuresis with other, mainly daytime, lower urinary tract symptoms [3]. The aetiology of NE has been attributed to multifactorial pathophysiological factors such as an altered antidiuretic hormone profile with nocturnal polyuria, arousal failure, delayed bladder maturation and nocturnal detrusor overactivity [4, 5]. Common co-morbidities identified with NE are: constipation, diabetes mellitus, developmental attention or learning difficulties, history of recurrent urinary tract infection (UTI) in boys, and pinworm infestation [6–8]. Current NE international prevalence rates are reported as between 5 and 20% of children over 5 years old [4, 7, 9–11] with an incidence as high as 18.2% in an Australian school-aged children cohort. Predictive or risk factors which have been linked with NE include: age, male gender, daytime incontinence, encopresis, social concerns, delayed age of walking, positive parental history of enuresis, and sibling history of enuresis [7, 9, 12].

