#### Eligibility criteria

The target population for this study is children aged between 6 and 14 years old (males and females) who have primary nocturnal enuresis ≥3 per week (wet nights). Potential participants will be excluded if they report a diagnosis of vesicoureteral reflux, spinal dysraphism, recent urotherapy, recent or current urinary tract infection (< 1 week), active cancer with current treatment, a history of cardiac failure and a history of renal disease or urinary retention.

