#### Interventions

##### Active intervention

Each capsule contains 420 mg of a proprietary blend of Urox® (Seipel Group, Brisbane, Australia) containing Cratevox™ (*Crataeva nurvala* L; Capparidaceae; Varuna) stem bark extract standardised for 1.5% lupeol: non-standardised *Equisetum arvense* L. (Equisetaceae; Horsetail) stem extract; and, non-standardised *Lindera aggregata* Sims. The TGA Approval number for the product is – AUSTL 194355. Capsules were manufactured in a Therapeutic Goods Administration licensed facility according to the PIC/S Guide to Good Manufacturing Practice for Medicinal Products, PE 009–9-15 January 2009. Capsules were subjected to microbiological and heavy metal testing to ensure they complied with product specifications.

The adult dose is two capsules per day taken once daily with food. The dosage is 1 capsule in the morning (< 40 kg) or 2 capsules in the morning (> 40 kg) for children. The dosage regimen was determined based on several integral methods as follows; earlier research with *Crataeva* and *Equisetum* alone [31, 32] and more recently with Schoendorfer, et al’s trial [30] with Urox which includes the newer formulation with 3 ingredients; pharmacopeia and traditional herbal medicine textbook dosage recommendations [33, 34] and Clark’s rule for dosage in Children (Dose = Adult dose x Weight(kg) / 70) which is conservative and tends to underestimate the required dose [35]. Urox was listed on the ARTG 6th February, 2012 and was marketed in Australia from this date. The Bedtime Buddy is the same formula as Urox but dosed for children and was listed with the TGA on the 14th June, 2017 – AUSTL 290162.

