##### Placebo

The active intervention will be compared with an identical vegetarian capsule containing colour-matched cellulose to that of the active ingredient. Participants will be prescribed 1 capsule in the morning (< 40 kg) or 2 capsules in the morning (> 40 kg).

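### The 6–14 age limit does not justify unstratified randomisation; capsule band should be a pre-specified covariate in the week-8 model (minor)

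*Protocol article*

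**What the plan says.** Under Methods: assignment of interventions, the protocol article states: "A block randomisation allocation was used based on 10 blocks of eight with an allocation of 1:1". It adds: "Two extra blocks of eight were generated for over 80 allocations". Sequence generation gives one reason for having no strata: "No stratification was implemented due to the specified age restriction of ages 6–14".

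Three other places bear on that reason:
- **Background:** "Predictive or risk factors which have been linked with NE include: age, male gender, daytime incontinence".
- **Active intervention:** "The dosage is 1 capsule in the morning (< 40 kg) or 2 capsules in the morning (> 40 kg) for children". The Placebo section applies the same weight rule. Table 1 repeats it but puts a child of exactly 40 kg in the one-capsule group, whereas the two intervention sections leave that weight unassigned.
- **Statistical methods:** "Groups will be compared at baseline and if difference(s) is/are ascertained, the variable(s) will be entered into the regression model". Neither age nor weight band is named there as a covariate.

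Height and weight are recorded at baseline (Case report form). The form is completed first at the Week 0 visit, and allocation takes place at that same visit (Week 0; Implementation).

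**The concern.** The stated reason treats an eligibility limit as if it produced a homogeneous sample. The article's own rules say otherwise: a 40 kg cut that decides between one and two capsules is needed only if children are expected on both sides of it. Capsule band marks body size, and with it probably age, as well as the number of capsules taken.

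A single list of 4:4 blocks balances the arm totals but not the arms within each band, so the band mix per arm is left to chance. At stake is some precision and face validity in a trial of 80 children. The only backstop is an adjustment rule that depends on what the baseline comparison happens to show.

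**Working it through.** **Inputs from the article.** Target 80 children, 1:1, so 40 per arm; blocks of eight; 20% attrition; 80% power; 5% two-sided significance. **Assumed, because the article gives no figure:** the share of children in the two-capsule band (25–50%), and the effect of band on the outcome (0.3–0.8 SD).

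**1. The plan's own figure.** The list matches the target: 10 × 8 = 80, or 96 with the two extra blocks. Attrition is consistent: 80 × 0.8 = 64 evaluable, 32 per arm. The 80 itself cannot be reproduced, since no effect size or SD is stated. At 32 per arm the implied detectable difference is (1.960 + 0.842) × √(2/32) = 0.70 SD.

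**2. Chance imbalance in band.** If K of the 80 children are in the two-capsule band, the number X falling in one arm is hypergeometric (80, K, 40), and the gap in shares is |2X − K|/40.

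| K (share) | P(gap ≥ 10 points) | P(gap ≥ 20 points) |
|---|---|---|
| 20 (25%) | 44% | 7% |
| 26 (32.5%) | 47% | 9% |
| 27 (about one third) | 34% | 6% |
| 28 (35%) | 48% | 10% |
| 40 (50%) | 50% | 12% |

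The dip at K = 27 is a parity effect. With an odd K a gap of exactly 4 or 8 children cannot occur, so the smallest gap counted in the 10-point column is 5/40 = 12.5 points. The low ends of the ranges (34% and 6%) come from that row; even values of K in this range give 44–50% and 7–12%.

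**3. Effect of stratifying.** In simulations of blocks of eight (10,000 runs each; shares of 20%, 30% and 40%), the SD of the gap was 8.9–11.0 points without strata and 2.2–2.5 points with blocks run within band. No stratified run reached 10 points.

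**4. Consequence for week 8.** Shift = gap × band effect.
- 10-point gap: 0.10 × 0.3 to 0.10 × 0.8 = 0.03 to 0.08 SD, or 4–11% of 0.70 SD.
- 20-point gap: 0.20 × 0.3 to 0.20 × 0.8 = 0.06 to 0.16 SD, or 9–23% of 0.70 SD.

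**5. Would the baseline comparison pick up such gaps?** The article does not say what counts as an ascertained difference. Suppose it means a 5% test (assumption). Uncorrected chi-squared for 20-point gaps:
- 16/40 v 8/40: 80 × (16×32 − 24×8)² / (40×40×24×56) = 3.81, p = 0.051 (Fisher 0.087).
- 24/40 v 16/40: 80 × (24×24 − 16×16)² / (40×40×40×40) = 3.20, p = 0.074 (Fisher 0.117).
- 14/40 v 6/40: 80 × (14×34 − 26×6)² / (40×40×20×60) = 4.27, p = 0.039.

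So a 20-point gap is sometimes caught and sometimes not. A 10-point gap is well short of the threshold: 12/40 v 8/40 gives 80 × (12×32 − 28×8)² / (40×40×20×60) = 1.07, against a critical value of 3.84.

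**The case against.** The case for leaving the design alone is substantial. Unstratified permuted blocks at a single site are a legitimate choice, and chance imbalance is already reflected in the standard error and p-value. The Background ties age to having enuresis. It does not say that age or weight predicts week-8 change among children who already wet on at least three nights a week, and a change-from-baseline outcome removes part of any difference in starting level. The article also has an adjustment rule. All of this stands, and it keeps the point minor.

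Three stronger readings are tempting and are not supported:
- **That the comparison is biased or invalid.** It is neither; the possible loss is in balance and precision.
- **That capsule number is confounded with treatment.** Placebo follows the same weight rule, so it is not. The overall mix of bands depends on who is recruited; stratifying would only make it similar between arms.
- **That the list must be rebuilt.** It has already been generated and sealed, a mid-trial change would help only later children, and a covariate handles band in the analysis without touching the envelopes.

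Two things survive the objection. The written reason is wrong on the article's own terms, and the adjustment rule depends on an observed difference, so it does not settle in advance whether band enters the model.

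**Conclusion.** The point holds as a minor one. The age limit does not support the decision not to stratify, and with 40 per arm a visible imbalance in capsule band is quite likely: roughly 34–50% for 10 points or more and 6–12% for 20 points or more. Those figures rest on an assumed 25–50% of children in the two-capsule band.

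The expected damage is small: 0.03–0.16 SD for gaps of 10 to 20 points, under an assumed band effect of 0.3–0.8 SD, against an implied detectable difference of about 0.70 SD. If band has little bearing on week-8 change, the shift is smaller still. The statement that the baseline rule can miss such gaps rests on reading it as a 5% test. The reason for acting is that the remedy costs almost nothing, not that the result would otherwise be unsafe.

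**What to change.** 1. Reconcile the Active intervention and Placebo sections with Table 1 on a child of exactly 40 kg, so that every child has one defined band. Which wording is right is for the investigators to settle.
2. In Statistical methods, name capsule band, taken from the weight recorded at Week 0, as a fixed covariate in the week-8 model whatever the observed baseline difference. For this factor it replaces the difference-triggered rule.
3. Delete the age-restriction reason from Sequence generation and state simply that allocation was blocked and unstratified.
4. Optional, if enough children are still to be randomised: finish the block in use, then assign whole unused blocks to one band or the other. Each block is already 4:4, so no new sequence is needed. Even for all 80 children, two series need at most 11 blocks, and the list holds 12.

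**Cost:** one degree of freedom and a short amendment. The optional step adds a second envelope series to manage and possibly one more incomplete block at the end.
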